### Adverse event reporting and safety

2.20

All adverse events will be recorded and discussed at weekly safety meetings by at least 2 investigators. If clinically indicated, the nature of the analgesia administered in the study may be revealed. After assessment by the Principle Investigator, any SAEs will be reported to the Ethics Committee in PUMCH. All SAEs will be also reported to the China Food and Drug Administration by the Ethics Committee.

### Data analysis

2.21

Data distribution will be tested for normality using the Shapiro–Wilk test. Skewed data will be corrected by logit-transformation as appropriate and subsequently examined using parametric test in order to preserve statistical power. For data set that cannot be normalized by logit-transformation, nonparametric test will be applied. Group comparison will be done by Student *t* test and Mann–Whitney *U* test for parametric and nonparametric data, respectively. Pearson Chi-square will be used for categorical variables. In strata where the expected counts are less than 5, Fisher exact test will be used. Univariate logistic regression and simple linear regression will be performed to determine potential predictors associated with binary outcomes and continuous outcomes, respectively. For predictors significantly associated with the outcomes of interest (*P* < .1), they will be further examined for co-linearity using Chi-square test, 0-order Pearson product-moment correlation, or Student *t* test as appropriate. For continuous variables with variable inflation factor greater or equal to 10, only 1 variable will be kept for subsequent analysis. After removing redundant co-variates, multivariate regression models will be built. The goodness-of-fit of the final models will be determined by the Hosmer–Lemeshow test (logistic regression) or *R*^2^ (multiple linear regression), respectively. For time-to-event outcomes, multivariate Cox proportional hazard regression models will be built. The cumulative probability of an outcome event over time will be presented in form of Kaplan–Meier curves.

To determine changes of analgesic consumption and pain score over time between groups, a generalized estimating equation population average regression will be used. To correct for ceiling effect of analgesic consumption on pain score reporting, an empirical logit transformation will be applied in before comparison between groups. For missing data less than 10%, imputation will be performed using median for continuous and ordinal variables. For nominal variables, the most common category will be imputed. If there are more than 10% missing data, multiple imputation will be used. Intention-to-treat and per-protocol analyses will be performed to account for possible missing data. *P*-value less than .05 will be considered as statistical significance. All statistical analyses will be 2-tailed and performed using Statistical Package for Social Sciences (SPSS version 24.0, Chicago, IL).

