**Table 1 T1:**
[figure not shown]
Data collection schedule.

The VAS has been used extensively for rating pain intensity in previous studies.^[15–17]^ Postoperative pain at 6, 12, 24, 36, 48, and 72 hours after surgery will be recorded using the VAS pain scores. The VAS consists of a 10-cm horizontal line with 1-cm vertical lines at each end on which a score of 0 indicates no pain and a score of 10 indicates the worst conceivable pain. All data are verified against original documents by individuals who are independent of the trial.

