#### Sufentanil consumption

2.16.1

Sufentanil consumption of IV-PCA during the first 48 hours postoperatively will be recorded.

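### The only transformation named for skewed data does not fit the consumption outcomes or unscaled VAS, and a normality test is left to set the primary effect scale

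*Protocol article*

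**What the plan says.** Section 2.21 (Data analysis) of the protocol article sets out a sequence. First, "Data distribution will be tested for normality using the Shapiro–Wilk test". Next, "Skewed data will be corrected by logit-transformation as appropriate and subsequently examined using parametric test in order to preserve statistical power". Then, "For data set that cannot be normalized by logit-transformation, nonparametric test will be applied". The comparison follows from the outcome of these steps: "Group comparison will be done by Student *t* test and Mann–Whitney *U* test for parametric and nonparametric data, respectively". The sequence is not limited to particular outcomes, except that time-to-event outcomes have their own Cox and Kaplan–Meier provision.

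The second paragraph of section 2.21 plans a generalized estimating equation (GEE) model for pain and consumption over time. It also says that an empirical logit will be applied before groups are compared, to deal with a ceiling effect on pain reporting. It does not define that transformation.

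The outcomes concerned are the average VAS pain score to day 3 (section 2.15), on a scale where "a score of 0 indicates no pain and a score of 10 indicates the worst conceivable pain"; sufentanil, for which "Sufentanil consumption of IV-PCA during the first 48 hours postoperatively will be recorded"; and the frequency and total dose of tramadol over 72 hours (section 2.16.3). Section 2.21 also selects covariates for multivariable models by a univariate screen: "For predictors significantly associated with the outcomes of interest (*P* < .1), they will be further examined for co-linearity".

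**The concern.** Two things are wrong with the stated rule. First, its only remedy for skewness is a function that the consumption outcomes cannot enter. Opioid and rescue totals are the variables most likely to be skewed, so the rule would be called on exactly where it fails, and the analyst would have to improvise after seeing the data.

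Second, the scale of the primary comparison is not fixed. A difference in mean VAS, a difference on the logit scale and a rank comparison answer different questions. Section 2.17 sizes the trial on the first of these, but section 2.21 lets a small-sample normality test choose among the three, and the empirical-logit sentence adds a further candidate scale. The trial could therefore report a primary effect that cannot be set against the difference it was designed to detect.

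**Working it through.** **Inputs (all from the protocol article).** VAS 0 to 10 (section 2.14.1). Sufentanil bolus 2 μg, 15-minute lockout, no basal infusion, pump removed at 48 h (section 2.10). Tramadol 50 mg each time (section 2.13). Planned 72-hour means 2.5 and 5.0, SD 2.5, two-sided alpha 0.05, power 80%, 14 per group, 18 after 20% dropout (section 2.17).

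**1. Design scale.** The planned difference is 5.0 − 2.5 = 2.5 raw VAS points, or 2.5/2.5 = 1.0 SD. The normal formula gives n = 2(1.960 + 0.842)² × (2.5/2.5)² = 15.7, so 16 per group. The exact two-sided t calculation gives 16.7, so 17. The stated 14 is not reproduced two-sided; it matches a one-sided t test (13.1, so 14). Dropout: 14/0.8 = 17.5, so 18, as stated. The mismatch is a separate matter. What counts here is that the design scale is the raw mean difference.

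**2. Domain of the logit.** logit(y) = ln(y/(1 − y)) needs 0 < y < 1.
- Sufentanil totals are 0, 2, 4, … μg: minus infinity at 0, undefined at every other value.
- Tramadol totals are 0, 50, 100, … mg: the same.
- Raw VAS is undefined above 1, including the pilot and planned means 2.1, 2.5, 5.0 and 5.6.
- VAS/10 works inside the range (2.5 gives −1.10; 5.0 gives 0) but is infinite at 0 and 10.
- Sufentanil has an implied ceiling of 48 × 4 = 192 boluses, or 384 μg, so it could be rescaled. Section 2.21 does not do this. Tramadol has no stated maximum.

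**3. The empirical logit.** With an assumed constant of 0.5, ln((x + 0.5)/(10 − x + 0.5)) is −3.04 at 0 and +3.04 at 10, so it is finite at the bounds. Applied to the two planned means, for illustration only, the contrast is 2.5 points raw, 1.10 on the logit of VAS/10, and 0.98 on this empirical logit.

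**4. How often the scale changes.** The sequence was simulated with 14 per arm and 6,000 runs. Shapiro–Wilk was applied in each arm at 0.05, the logit step used the 0.5 constant, and a t test or Mann–Whitney test followed. At means 5.0 and 2.5:

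| Data model | Raw t test | Logit t test | Mann–Whitney | Not raw |
|---|---|---|---|---|
| Normal, SD 2.5, clipped to 0–10 | 76% | 11% | 14% | 24% |
| Beta-shaped on 0–10 | 58% | 34% | 8% | 42% |

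(The first row sums to 101 through rounding; unrounded, 75.75 + 10.67 + 13.58 = 100.) Even with exactly normal data in both arms, two tests at 0.05 would reject at least once in 1 − 0.95² = 9.75% of trials.

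**5. Type I error.** With equal means of 5.0 or 2.5, the sequence rejected in 5.0% and 5.4% of trials (clipped normal; fixed t test 5.0% and 5.3%), and in 5.8% and 6.0% (beta; fixed t test 5.7% and 5.5%). At the planned difference with clipped normal data, power was 70.8% against 71.1% for the fixed t test.

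**6. Covariate screen.** The number of candidates is not given. With an assumed 5 to 15 independent candidates unrelated to the outcome, the chance that at least one passes P < .1 is 1 − 0.9⁵ = 41% to 1 − 0.9¹⁵ = 79%.

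**The case against.** The text is softer than a blanket instruction. The logit applies only where judged appropriate, and data that it cannot normalise go to a nonparametric test. For sufentanil and tramadol that ends in Mann–Whitney, which is also the test recommended below. An article may also leave rescaling and constants to a full plan. All of this stands, and it lowers the practical cost for consumption outcomes. It does not repair the rule: the one transformation named cannot be tried on those outcomes as written, and nothing in the fallback fixes the scale of the primary comparison.

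A reader might infer four stronger points that the document does not support.
- **Patients with no pain are discarded.** Under a normal model, 16% of single cocktail-arm scores fall at or below 0 with the planned values (9% with the pilot values). These figures concern one time point. The primary outcome is an average and is 0 only if every score is 0. An empirical logit is normally finite at 0 and 10, and no section says that such values are dropped.
- **Time to first PCA use is put through the logit.** Section 2.21 sends time-to-event outcomes to Cox regression and Kaplan–Meier curves.
- **Treatment could be screened out at P < .1.** The screen serves to identify predictors. Nothing says that treatment passes through it, or that these models replace the two-group comparison.
- **The P value becomes unreliable.** The simulated error rates differ little from those of a fixed t test.

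**Conclusion.** The point holds in a limited form. Section 2.21 names a transformation that does not fit the consumption outcomes or unscaled VAS, adds a second, undefined logit, and leaves the primary effect scale to a normality test with 14 to 18 patients per arm. At the planned means, about one trial in four would not report the raw mean difference on which the sample size rests; type I error is barely affected.

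The one-in-four figure assumes clipped normal data, testing in each arm at 0.05 and a 0.5 constant. It also applies the planned 72-hour mean and SD to the averaged outcome. An average of six assessments may be closer to normal, which would lower the figure; beta-shaped data raised it to 42%. That the scale is not fixed in advance does not depend on any of these assumptions. The correction should be made before the data are analysed, and it does not call the design into question.

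**What to change.** In section 2.21:
- Delete the Shapiro–Wilk and logit branch, and the empirical-logit sentence in the second paragraph.
- Analyse the average VAS untransformed by one named method: a t test, or a linear model with treatment, giving a mean difference and 95% CI. State Mann–Whitney as a sensitivity analysis and the GEE over time as secondary.
- Compare sufentanil and tramadol by Mann–Whitney with a Hodges–Lehmann estimate.
- State that the P < .1 predictor models are exploratory, and that any adjusted treatment comparison always contains treatment plus one or two covariates fixed in advance.

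The cost is a change of wording. The small downside is less freedom to adapt the test to the data.

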#### Data capture

2.14.1

Schedule for data collection is shown in Table 1. Specifically, the following data will be collected – demographic information, daily visual analog scale (VAS) pain score, sufentanil consumption, time to first use of IV-PCA, postoperative nausea and vomiting, rescue analgesia consumption, all other side effects and complications.

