### Sample size

2.17

The sample size calculation was based on the following parameters:

(1)alpha value = 0.05, 2-sided;(2)power = 80%.

The minimal clinical significance in VAS pain score was defined as the mean difference between current and preceding scores when the subject reported “a little worse” or “a little better” pain. Our pilot study shows that VAS pain scores 72 hours after lumbar spinal fusion surgery were reported to be 2.1 ± 1.6 in patients receiving cocktail analgesic injection and 5.6 ± 1.7 in patients without. Based on these findings, we hypothesized that VAS pain score 72 hours after surgery will be 2.5 for the cocktail group and 5.0 for the control group, with a standard deviation set at 2.5 and a ratio of patients in the cocktail to the control group of 1:1. Calculations showed that a sample size of 14 patients per group to detect a difference in VAS pain score between the 2 groups after treatment. Assuming a 20% dropout rate, 18 patients per group, or a total of 36 patients, are required.

It is anticipated that recruitment for this study will take 6 months to complete, using 1 surgeon to reduce surgical variability. Data collection for each patient will occur during the first 72 hours postoperatively and at a routine 4-week follow-up appointment. No further follow up will be routinely arranged. Any patients requiring specific follow up will have this arranged on an individual basis.

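### In a 36-patient trial, one covariate fixed in advance (preoperative VAS) would be a cheap improvement on unadjusted tests plus a P < .1 covariate screen, with a gain that depends on an unstated correlation

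*Protocol article*

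**What the plan says.** Section 2.21 (Data analysis) of the protocol article gives a general rule for comparing the arms: "Group comparison will be done by Student" t test, or by Mann-Whitney U test if the data cannot be normalised. Neither uses a covariate. The section then describes univariate regressions to look for predictors. "For predictors significantly associated with the outcomes of interest" at P < .1, it checks collinearity and builds multivariable models. Its second part adds a GEE for pain score and analgesic consumption over time between groups, again with no covariate named.

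Section 2.15 defines the primary outcome as the average incision-site pain score up to postoperative day 3. The text does not say which of these methods is its primary analysis.

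On measurement, section 2.14.1 lists "demographic information, daily visual analog scale (VAS) pain score" among the data collected, and the text under Table 1 states "Postoperative pain at 6, 12, 24, 36, 48, and 72 hours after surgery will be recorded using the VAS pain scores". The text mentions no preoperative VAS. The content of Table 1 could not be read for this review, so it is open whether one is scheduled.

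**The concern.** With 14 to 18 patients per arm, chance differences in baseline pain are common. An unadjusted test leaves their effect in the treatment estimate, to the extent that baseline pain predicts the outcome. A prognostic covariate fixed in advance removes that part and reduces residual variance without enrolling anyone.

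The only route to adjustment that the plan describes depends on the trial data. A P < .1 screen in about 30 patients will often drop a covariate that is moderately useful and sometimes keep one that is useless. If that route is used for the treatment comparison, the adjusted estimate rests on a choice made after the data are seen.

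What is at stake is precision and a clear prespecified estimate. The validity of the test is not in question.

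**Working it through.** **Inputs.** From section 2.17: "alpha value = 0.05, 2-sided"; power 80%; "VAS pain score 72 hours after surgery will be 2.5 for the cocktail group and 5.0 for the control group", a difference of 2.5; "with a standard deviation set at 2.5"; "a ratio of patients in the cocktail to the control group of 1:1"; 14 per group, raised to 18 for 20% dropout. The correlation r between preoperative and postoperative VAS within groups is not given, so it is an assumption, shown from 0 to 0.6.

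**The plan's own figure.** For a two-sample t test the noncentrality is 2.5 / (2.5 × √(2/n)).
- n = 14: 2.646 on 26 df, critical value 2.056, power 72.1%.
- n = 17: power 80.7%, the smallest n that reaches 80%.
- n = 18: noncentrality 3.000 on 34 df, power 83.0%.

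The stated 14 is therefore not reproduced two-sided; a one-sided t calculation does give 14. That is a separate sample-size matter. It is noted here only because 72.1% and 83.0% are the reference values below.

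**One prespecified covariate.** With N = 2n, the variance of the treatment estimate is multiplied by (1 − r²) × (N − 3)/(N − 4), and the df fall to N − 3. Example, n = 14 and r = 0.5: factor 0.75 × 25/24 = 0.781; noncentrality 2.646/√0.781 = 2.993 on 25 df; power 82.0%.

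| r | 14 per arm | 18 per arm |
|---|---|---|
| Unadjusted t test | 72.1% | 83.0% |
| 0 | 70.3% | 81.8% |
| 0.2 | 72.0% | 83.3% |
| 0.3 | 74.3% | 85.2% |
| 0.4 | 77.6% | 87.9% |
| 0.5 | 82.0% | 91.2% |
| 0.6 | 87.6% | 94.8% |

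Simulation (20,000 runs per case) at r = 0, 0.3 and 0.5 agrees within 0.7 points: 70.9%, 74.0% and 82.1% at 14 per arm; 81.4%, 85.3% and 91.3% at 18. Break-even for power is at r of about 0.21 (14 per arm) and 0.18 (18 per arm).

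**The P < .1 screen.** Simulation (40,000 runs per case) regressed the outcome on the covariate alone, with the planned 1-SD group difference present.

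| True r | Kept, 14 per arm | Kept, 18 per arm |
|---|---|---|
| 0 | 10% | 10% |
| 0.3 | 40% | 48% |
| 0.4 | 60% | about 70% |
| 0.5 | 79% | about 87% |

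Part of the loss arises because the screen ignores group. The treatment difference adds 0.25 to an outcome variance of 1, so a within-group r of 0.3 appears as 0.3/√1.25 = 0.27.

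**Chance imbalance.** The standard error of a baseline difference is √(2/14) = 0.38 SD at 14 per arm and √(2/18) = 0.33 SD at 18. An imbalance of 0.5 SD or more occurs in about 19% and 13% of trials respectively. It enters the estimate scaled by r: with SD 2.5, a 0.5-SD imbalance shifts the difference by 0.5 × 0.3 × 2.5 = 0.375 VAS points at r = 0.3, and by 0.5 × 0.5 × 2.5 = 0.625 at r = 0.5.

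**The case against.** The case against is substantial, and most of it stands as a limit on the point.

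- An unadjusted test is valid in a randomised trial. A reader might infer that the plan is wrong to use one; it is not.
- A reader might infer that the t test is the primary pain analysis. Section 2.21 states it generically and also assigns pain over time to a GEE, so this is not settled.
- The P < .1 step can be read as secondary predictor modelling and not as adjustment of the treatment effect. The text allows both readings.
- A reader might infer that no preoperative VAS is collected. The readable text mentions none, but Table 1 could not be read, so neither presence nor absence can be asserted.
- Preoperative pain here comes from stenosis or disc herniation, whereas the outcome is incision pain. They are different pains, r may be low, and below about 0.2 there is no gain.
- The power inputs are for VAS at 72 hours, not the 3-day average. If the six readings each have SD 2.5 and correlate at 0.5 to 0.9, and the difference is the same, the SD of the average is 2.5 × √((1 + 5 × 0.5)/6) = 1.91 to 2.5 × √((1 + 5 × 0.9)/6) = 2.39. Unadjusted power at 14 per arm is then about 92% to 76%. With the larger pilot SD of 1.7 it is already 96%, and adjustment at r = 0.3 gives 97%.

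Choosing a covariate is often left to the analysis plan. This article, however, does more than stay silent: it writes down unadjusted comparisons and a data-driven route for covariates. A better method can fairly be set against that.

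**Conclusion.** This is a low-cost improvement, not an error. The plan's only stated way of bringing in covariates is unreliable at this sample size, and one covariate fixed in advance is better.

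On the 72-hour inputs at 14 per arm, the change in power runs from a loss of about 2 points (r = 0) through nothing (r about 0.2) and a gain of about 2 points (r = 0.3) to gains of about 10 (r = 0.5) and 15 to 16 (r = 0.6). At 18 per arm it runs from a loss of about 1 point to a gain of about 12. These figures assume a linear relation, a common SD and an r that the documents do not supply. Absolute power for the 3-day average will differ.

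Two stronger claims are not supported. Adjustment cannot be said to gain power outright, because that depends on r. Nor should it be presented as repairing the sample size: reaching 80% with 14 per arm would need r near 0.5, which nothing in the documents establishes.

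**What to change.** In section 2.21:

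1. Name one primary analysis of the average postoperative VAS: a linear model on group, with preoperative VAS as the single prespecified covariate, kept whatever its P value.
2. Report the unadjusted t or Mann-Whitney comparison as a sensitivity analysis, and say whether the transformation steps apply to the primary model or only there.
3. Carry the same covariate into the GEE.
4. Limit the P < .1 screening to exploratory predictor models.

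If Table 1 schedules a preoperative VAS, use it. If not, take one mark on the same 10-cm scale before surgery.

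The cost is a few sentences of analysis text, one degree of freedom (at most about 2 points of power, if preoperative and postoperative pain are unrelated) and at most one VAS mark per patient. Enrolment and treatment do not change.

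### Covariates for the adjusted logistic and linear models are picked by a P < .1 screen in 36 patients with no guaranteed place for treatment group, and time to first IV-PCA use has no named unadjusted test

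*Protocol article*

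**What the plan says.** Section 2.21 of the protocol article first sets unadjusted group comparisons: Student t or Mann–Whitney for continuous data, and chi-square or Fisher for categorical data. It then moves to regression:

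- Screening: "Univariate logistic regression and simple linear regression will be performed to determine potential predictors associated with binary outcomes and continuous outcomes".
- Retention: "For predictors significantly associated with the outcomes of interest" at P < .1, a collinearity check follows and redundant variables are removed.
- Final model: "After removing redundant co-variates, multivariate regression models will be built".
- Time-to-event outcomes: "For time-to-event outcomes, multivariate Cox proportional hazard regression models will be built", with Kaplan–Meier curves for presentation.

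The second paragraph of the section adds a GEE model comparing pain score and analgesic consumption over time between groups. The candidate predictors are not listed. Nothing says whether treatment group is always in the regression models or must itself pass the screen. Time to first IV-PCA use is a secondary outcome (Section 2.16.2).

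**The concern.** Randomisation already makes the unadjusted comparison valid. Adjustment helps when covariates are chosen beforehand because they are expected to predict the outcome. Here they are chosen because they happened to correlate with the outcome in this sample. The adjusted estimate then depends on which chance associations crossed P < .1, and its standard error takes no account of the selection. If group is not always included, a reported multivariable model might not contain the comparison the trial was built for.

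The time-to-event outcome raises a different problem. The Cox sentence states no screening rule, but it commits the analysis to an adjusted model without naming an unadjusted test beside it. What is at stake is whether the adjusted and time-to-event results can be reproduced from the plan, not the validity of the primary comparison.

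**Working it through.** **Inputs**

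- Size: "Assuming a 20% dropout rate, 18 patients per group, or a total of 36 patients, are required". Evaluable size: "Calculations showed that a sample size of 14 patients per group to detect a difference in VAS pain score between the 2 groups" (Section 2.17).
- Planned effect: "VAS pain score 72 hours after surgery will be 2.5 for the cocktail group and 5.0 for the control group", with SD 2.5, so (5.0 − 2.5)/2.5 = 1.0 SD.
- Screening threshold: P < .1 (Section 2.21).
- Number of candidates: not given. Assumed range 5 to 15.

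**The plan's own figure.** The dropout step reproduces: 14/(1 − 0.20) = 17.5, rounded up to 18 per group, 36 in all. The 14 does not follow from the stated two-sided alpha of 0.05 and 80% power: 2 × (1.960 + 0.842)² × (2.5/2.5)² = 15.7, so 16 per group, or 17 by the exact t method. That mismatch is a separate matter. Here 14 and 18 per group serve only as the two sizes to examine.

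**Chance selection.** Each independent noise covariate passes with probability 0.1, so P(at least one of k) = 1 − 0.9^k and the expected number is 0.1k.

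| Candidates k | P(at least one enters) | Expected number |
|---|---|---|
| 5 | 1 − 0.9^5 = 41% | 0.5 |
| 10 | 1 − 0.9^10 = 65% | 1.0 |
| 15 | 1 − 0.9^15 = 79% | 1.5 |

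**Effect on the adjusted comparison.** Simulation of the linear model: 6,000 trials per setting, independent noise covariates, each screened alone against the outcome at P < .1, treatment group always kept in, two-sided 0.05. Power at 1.0 SD (losses taken before rounding):

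| Per group | Candidates | Unadjusted | Screened, group kept | Loss (points) |
|---|---|---|---|---|
| 14 | 5 | 72.6% | 69.4% | 3.2 |
| 14 | 10 | 73.0% | 66.4% | 6.7 |
| 18 | 5 | 82.5% | 79.9% | 2.6 |
| 18 | 10 | 82.8% | 77.8% | 5.0 |

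With no treatment effect, the adjusted test rejected in 4.7% to 5.4% of trials across the same four settings, so the screen does not inflate type I error. Power falls because the univariate screen ignores group. When treatment works, a noise covariate that is imbalanced between groups by chance correlates with the outcome, is favoured for selection, and then takes part of the treatment effect.

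**If group itself had to pass the screen** (a condition the text does not state). P(fail) = 1 − power of a two-sided t test at alpha 0.10, with noncentrality 1.0 × √(n/2). At 18 per group (noncentrality 3.0) this is 9.8%; at 14 per group (2.65) it is 17.6%.

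**Which comparisons have a route outside the screen**

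- Pain score and sufentanil consumption: t or Mann–Whitney, and the GEE.
- Binary outcomes, such as nausea: chi-square or Fisher.
- Time to first IV-PCA use: for time-to-event outcomes only the multivariable Cox model is named. Kaplan–Meier curves are descriptive, and no log-rank test appears.

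**The case against.** The strongest reply is that the screened regressions serve a different purpose. They are introduced as a search for predictors, after the group tests have been set out, and nothing presents them as the estimate of treatment effect. On that reading they are a secondary analysis that lacks only an exploratory label. An article may also leave the candidate list and the Cox covariates to a fuller plan.

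Much of this stands. The group comparisons are specified independently of the screen, and a missing covariate list is not in itself a fault. But the screening rule is not missing detail: it is stated, and it is a poor rule for any model used to report a treatment effect. The article does not confine it to exploratory use.

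A reader might infer several stronger things that the document does not support:

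- *The randomised comparison may be lost from the trial.* No sentence puts treatment through the screen, and the t, Mann–Whitney, chi-square, Fisher and GEE comparisons stand outside it. The 9.8% and 17.6% above are conditional on a reading the text leaves open.
- *The Cox covariates are screened too.* The screen is written for logistic and linear regression only.
- *Pain will be adjusted for analgesic use after randomisation.* The screening text does not name analgesic use as a candidate. The absence of a bar is not a plan to do it.
- *Type I error is inflated.* A rate of about 6.5% arises only if investigators report the better of the adjusted and unadjusted results. That is selective reporting, not a consequence of the rule.

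It can also be argued that the general t or Mann–Whitney rule covers time to first IV-PCA use. Section 2.16.2, however, also records a proportion of patients over 48 hours, which suggests that some may never use the pump. Those tests do not handle such censoring, and the sentence written specifically for time-to-event outcomes names only the Cox model.

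**Conclusion.** The point holds in a limited form and should be corrected. The adjusted logistic and linear models take their covariates from an outcome-based screen at P < .1 in 36 patients, with no assurance that group is included. The harm is an arbitrary covariate set and, with group kept in, about 3 to 7 points of power at the planned effect. Type I error stays near 5%.

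These figures assume independent, purely noise candidates: 5 to 15 for the selection probabilities, 5 to 10 for the power loss. The power figures are for the linear model. Genuinely prognostic covariates could offset the loss, but that argues for naming them in advance.

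The primary outcome is not at risk from this step. Time to first IV-PCA use is more exposed, because its only named inferential method is an adjusted model whose covariates the article does not state.

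**What to change.** Amend Section 2.21 as follows:

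- For any model that reports a treatment effect, drop the P < .1 screen, always include treatment group, and adjust, if at all, only for a few baseline covariates fixed in advance and retained whatever their P values.
- Compare time to first IV-PCA use by the log-rank test, and report a Cox hazard ratio with group only or with the same prespecified covariates.
- Keep the screened predictor models if they are wanted, but label them exploratory and do not use them for treatment conclusions.

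This changes analysis wording only, with no extra patients or data. The cost is giving up data-driven adjustment, so a strong predictor not foreseen in advance would be left out of the treatment-effect models.

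### For pairs involving a categorical variable, the only stated collinearity check is a significance test, which at 36 patients reacts to associations far too weak to make a covariate redundant

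*Protocol article*

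**What the plan says.** Section 2.21 (Data analysis) of the protocol article builds its regression models in steps. Candidate predictors are screened one at a time against the outcome at P < .1. Of those that pass, the text says "they will be further examined for co-linearity using Chi-square test, 0-order Pearson product-moment correlation, or Student" t test, as appropriate. The next sentence gives a numerical rule: "For continuous variables with variable inflation factor greater or equal to 10, only 1 variable will be kept for subsequent analysis". Then: "After removing redundant co-variates, multivariate regression models will be built".

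Three things are left open. The text attaches no P threshold and no action to the chi-square, Pearson and t tests; the only threshold on offer is the general P < .05 at the end of the section. It does not define redundancy for a pair in which at least one variable is categorical. It does not say whether study group is one of the predictors tested against the others, or which member of a flagged pair is kept.

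The planned size comes from section 2.17 (Sample size): "18 patients per group, or a total of 36 patients, are required".

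**The concern.** Collinearity matters when two covariates carry so nearly the same information that their coefficients cannot be estimated separately. A VIF measures that directly. A P value does not: it depends on sample size as well as strength of association, and it becomes small long before either variable is redundant.

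For continuous variables the VIF sentence supplies a sensible criterion. For sex, diagnosis, ASA class or any other categorical covariate, the reader has only a test result. Either significance decides, which is the wrong criterion, or nothing stated decides, and removal becomes discretionary.

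A particular hazard arises if study group enters this check. A t or chi-square test of a covariate against study group is a test of baseline imbalance. A significant result would then mark as redundant a covariate that has already been associated with the outcome and is out of balance between arms. That is the covariate for which adjustment is most useful. Since the text does not say which member of a pair survives, study group itself is not protected either.

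**Working it through.** **Inputs.** From section 2.17: 18 per group, 36 in total; 14 per group before inflation; difference 5.0 − 2.5 = 2.5 VAS points; SD 2.5. From section 2.21: VIF threshold 10, screen P < .1, general significance P < .05 two-tailed. Assumed: the general P < .05 applies to the collinearity tests; study group is among the tested predictors (steps 4 to 6 only); 5 to 10 candidate covariates; the covariate-VAS correlations given below.

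**1. The plan's own figures.** The inflation step reproduces: 14 / (1 − 0.20) = 17.5, so 18 per group and 36 in total. (With the stated inputs the two-sided normal approximation gives 2 × (1.960 + 0.842)² × (2.5/2.5)² = 15.7, so 16 and not 14 per group. That is a separate matter; this check takes 36 as the planned number.) For two predictors VIF = 1/(1 − r²), so VIF 10 means r² = 0.9 and |r| = 0.949.

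**2. Where the tests become significant.** The smallest significant correlation is r = t / √(N − 2 + t²).

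| N | two-sided P | smallest significant \|r\| | VIF |
|---|---|---|---|
| 36 | .05 | 0.329 | 1.12 |
| 36 | .10 | 0.279 | 1.08 |
| 28 | .05 | 0.374 | 1.16 |

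For N = 36 and P = .05: t(34) = 2.032, and 2.032 / √(34 + 4.130) = 0.329. The same threshold holds for a t test, which is equivalent to a correlation with a two-level variable. For a 2 × 2 chi-square without correction, phi = √(3.841/36) = 0.327.

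**3. How often the two criteria disagree.** In 20,000 simulated samples of 36 with a true correlation of 0.5 between two normal variables, 89% gave a significant correlation and none reached VIF 10.

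**4. If study group is tested.** With 18 per arm, a continuous covariate is flagged from 2.032 × √(2/18) = 0.68 SD between arms. Given significance, the mean absolute imbalance is 0.76 SD (simulation).

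**5. Chance of such a flag.** Without the outcome screen, the chance that at least one of 5 or 10 independent covariates is significantly imbalanced is 1 − 0.95⁵ = 0.226 or 1 − 0.95¹⁰ = 0.401. But only covariates associated with the outcome at P < .1 reach the collinearity check. A simulation with 18 per arm, a group effect of 1 SD (2.5/2.5) and 40,000 runs counted covariates that were both screened in and imbalanced at P < .05:

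- 5 covariates unrelated to VAS: about 6%
- 10 covariates unrelated to VAS: about 12%
- 5 covariates each correlated 0.3 with VAS: about 12%

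Losing an unrelated covariate does little harm, so the third line is the more relevant one.

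**6. Size of the shift if it happens.** Dropping an imbalanced covariate leaves about correlation × SD × imbalance unadjusted. At a correlation of 0.3 this is 0.3 × 2.5 × 0.76 = 0.57 VAS points, or 0.57/2.5 = 23% of the hypothesised difference. At 0.5 it is 0.95 points (38%). The upper value cannot go with five independent covariates at that strength, because they would imply R² = 5 × 0.25 = 1.25.

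**The case against.** The strongest reply is that the plan never says a significant test removes anything. Predictors are examined, the VIF sentence follows, and redundancy can be read as referring to that sentence alone. A condensed article may leave the criterion for categorical pairs to a fuller document. This stands in part: the removal rule is a reading, and for continuous pairs it would be a wrong one. A reader might infer that the plan discards any predictor correlated at about 0.33 with another. For continuous variables the VIF rule governs, so the text does not support that.

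What remains is that the article does name its tool for categorical and mixed pairs, and the tool does not measure the thing it is named for. That is a stated method, not an omitted detail.

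A second reply is that study group may not be in the predictor set at all, because section 2.21 sets out the group comparison separately. This also stands: the imbalance argument is conditional. Nothing in the text exempts study group, however, and in a two-arm trial it is an obvious candidate predictor.

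A third reply is that the efficacy comparison does not depend on these models. That is right for the t test or Mann-Whitney test, and nothing in the text says the generalized estimating equation uses this selection.

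**Conclusion.** The point holds in limited form and is a minor correction. For pairs involving a categorical variable, section 2.21 gives only a significance test as the collinearity check. At 36 patients that test responds from |r| of about 0.33 (VIF 1.12), or about 0.37 at 28 patients, against about 0.95 for the plan's own VIF of 10. If significance decides, weakly associated covariates would be dropped from the multivariable models.

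The further risk, removal of an imbalanced prognostic covariate or of study group, requires that study group be among the tested predictors, which is not stated. On that assumption the chance of at least one such flag is roughly 6-12% for 5-10 candidate covariates.

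Two stronger conclusions are tempting and not supported. One is that the chance is 23-40%; that ignores the P < .1 screen. The other is that the trial's main treatment comparison would move by up to 38% of the hypothesised effect. The shift in step 6 applies only to a multivariable model of pain score that includes study group and has lost the covariate, and it rests on assumed correlations.

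**What to change.** In section 2.21, delete the chi-square, Pearson and Student t tests as collinearity checks and use one rule for all covariates. Suggested wording: *Collinearity among covariates will be assessed by the variance inflation factor from the fitted model (generalised variance inflation factor for categorical variables), with a threshold of 10. Study group is always kept in the model and is not part of this check, and no covariate is removed because it is associated with study group.*

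The cost is two sentences and no new data. The small downside is that a model may keep one or two moderately correlated covariates.
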